## Abstract

**Background:**

Sleep is essential for children's health, cognitive development, academic performance, and overall well-being. Short sleep duration has been associated with several adverse outcomes, including an increased risk of obesity and impaired cognitive functions. Despite these associations, few studies have demonstrated causal links with these outcomes. Objective: To assess the effects of sleep extension on body weight regulation and learning ability in school-aged children with nocturnal sleep below recommendations for their age. Method: More2Sleep is a randomized, controlled, parallel trial involving 142 school-aged children (6–12 years old) who are “short-sleepers” (≤9 h/night). The children will be randomly assigned to a sleep extension group (by ∼45 min/night, achieved by going to bed 60–90 min earlier than usual; *n* = 71) or a control group (habitual sleep schedule; *n* = 71) guided by a family advisor for 12 weeks, followed by a 6-month inactive follow-up. All outcomes will be measured at baseline and 12 weeks. Selected outcomes will be reassessed at the 6-month follow-up to evaluate the sustainability of the intervention. Subgroups of children will undergo additional tests (substudy-I: metabolism and appetite; substudy-II: structural, functional, and diffusion MRI) to evaluate the mechanisms by which sleep may affect weight homeostasis and cognitive functions. Co-primary outcomes include the change in BMI z-score and learning ability from baseline to 12 weeks. Secondary outcomes include percent body fat, dietary energy intake, hunger and satiety, physical activity, energy expenditure, brain activity patterns, and cognitive and academic performance. Discussion: This study has broad implications as it can potentially inform future sleep recommendations and treatment strategies to reduce overweight/obesity and improve children's metabolic health and learning abilities.

**Clinical Trial Registration:**

https://clinicaltrials.gov/study/NCT06341179, identifier NCT06341179.

## Introduction

Sleep is essential to children's and adolescentś health and overall well-being (1–5). However, sleep duration among children and adolescents has declined over the past decades (6). Insufficient sleep is associated with a range of detrimental physical and mental outcomes, including increased risk of obesity (5, 7), inflammation (8), cardiovascular diseases (9–11), cognitive impairments (1), lower academic performance (1, 2, 12), and altered brain development (13).

Among these adverse outcomes, the relationship between insufficient sleep and obesity is particularly interesting. In parallel with a decrease in overnight sleep duration among children and adolescents (6), obesity rates have increased from 2% in 1990 to 8% in 2022 worldwide (14). In fact, there is a growing body of literature suggesting strong associations between short sleep duration and a greater risk of obesity in this age group (7, 15–19). Pooled results from cohort studies indicate that short sleep duration doubles the risk of overweight or obesity in children (7). Similarly, a meta-analysis found that children who sleep less than 10 h per night have nearly twice the odds of being obese compared to those who sleep longer (15). This association appears to be dose-dependent, with an additional meta-analysis demonstrating that each additional hour of sleep reduces the risk of overweight/obesity by 9% (16). Although these findings indicate that short sleep duration is a significant risk factor for weight gain and obesity early in life, the observational nature of these studies prevents inferences on causality.

Only a few experimental studies have investigated the effect of sleep duration manipulation on body weight homeostasis or eating behavior in school-aged children (20–22). A 3-week randomized crossover study in 37 children found that sleep restriction increased reported food intake (particularly sugary drinks), fasting leptin, and body weight relative to sleep extension. It also resulted in greater caloric intake in the evening (resulting in a delay in the timing of mean daily caloric intake and changes in sedentary and physical behaviors as well), albeit changes in physical activity were mixed (20, 23, 24). These results provide proof of concept that sleep duration is causally linked with obesity in children. They are, however, difficult to interpret as the two conditions (extension vs. restriction) differed by 141 min/night, which is unlikely to be achieved in real life. To further explore this, a subsequent parallel study of 78 children randomly assigned to either sleep extension or habitual sleep for 2 months (21). There were no significant changes in body weight or calorie intake between groups, but a combined analysis across groups showed that those who extended their sleep by at least 30 min/night consumed significantly fewer calories from fat and had a lower body mass index (BMI) z-score than those who did not increase their sleep (21). Secondary analyses further demonstrated that although there was not a direct effect of intervention on weight status, earlier bedtimes mediated the effect of intervention on child BMI z-score (25). Taken together, the findings of this study will support the idea that sleep extension may benefit weight management in children. However, additional experimental studies are needed to investigate the effects of sleep extension on body weight regulatory mechanisms in children.

Along with its impact on physical health, sleep duration is vital to brain and cognitive development, including learning ability, memory processes, and school performance (2, 12, 26–29). Short sleep duration has been consistently linked to poor school performance in children and adolescents (1, 2). Only few experimental studies have examined the role of sleep duration manipulation in cognitive development. In a crossover study, 77 children were randomized to 3 nights of 1 h sleep extension or restriction. Those who extended their sleep by at least 30 min improved their performance on digit forward memory and continuous performance tasks. In contrast, performance on a simple reaction time task significantly decreased in children who restricted their sleep by at least 30 min. This study also provided evidence that sleep quality (sleep onset latency, sleep percentage, night awakenings) is independent of sleep duration and may affect neurobehavioral functioning (30). Another study of 32 children with a very similar design (4 nights of 1-hour sleep extension or restriction after a week of habitual sleep in a crossover design) reported that children performed better on a battery of tests focused on emotion regulation, memory, attention, and math fluency after sleep extension vs. restriction (31). The results also demonstrated a noteworthy order effect: children who began with sleep extension performed better in memory and attention tasks than those who began with sleep restriction. Furthermore, exploratory findings by the authors showed that the overall difference in sleep duration between the two conditions was negatively associated with emotion regulation and aspects of attention related to inhibitory control.

Not only can sleep influence cognitive functions in children, but recent studies have also found that certain sleep behaviors (sleep timing, duration, and pattern) were related to gray matter volume in cortical and subcortical brain structures (32). A recent cohort study in preadolescents found that insufficient sleep (defined as less than 9 h/night) had adverse effects on both brain and behavior compared to those with sufficient sleep (33). Specifically, insufficient sleep had adverse effects on depression, thought problems, picture-vocabulary test performance, and crystalized intelligence. Furthermore, children with insufficient sleep also exhibited differences in cortical grey matter volume across 12 regions and in resting-state functional connectivity, especially in the basal ganglia, at baseline and at 2-year follow-up. A mediation analysis revealed that at baseline, the functional and structural brain measures mediated the effects of sleep duration on all behavioral measures. Longitudinally, the connectivity between the retrosplenial-temporal network and the right ventral dienchephalon mediated effects of sleep duration on picture-vocabulary test performance and crystallized intelligence (33).

The interconnectedness between sleep, weight status, and cognitive performance is illustrated by the results of a meta-analysis of 110 unique cohorts encompassing almost 600,000 healthy children and adolescents aged 5–17 years from 40 countries. This analysis indicates that shorter sleep duration is associated with higher adiposity indicators and poor academic achievement (5). However, as experimental studies are scarce, understanding the direction and magnitude of these associations and the underlying mechanisms remains elusive. Furthermore, it remains unclear whether extending sleep duration can mitigate the adverse effects of short sleep on weight status and cognitive function in children. This is crucial for developing effective strategies to improve children's health and overall well-being.

The More2Sleep study aims to fill this gap by investigating the potential beneficial effects of sleep extension by ∼45 min/night, achieved by going to bed 60–90 min earlier, on body weight homeostasis and learning ability in school-aged children with a shorter overnight sleep duration than recommended for their age (≤9 h/night). The secondary objectives are included to evaluate various relevant physiological processes that will provide mechanistic insights into the effects of sleep extension on body weight homeostasis, cognitive functioning, and academic performance.

## Methods and analysis

Methods reporting follows the *Standard Protocol Items: Recommendations for Interventional Trials* (SPIRIT) statement and the *Consolidated Standards of Reporting Trials* (CONSORT) guidelines. The complete SPIRIT checklist can be found in the online Supplementary Material.

### Study design

More2Sleep is a two-arm, parallel, randomized controlled trial in 142 children who are allocated in a 1:1 ratio to either an intervention group (*n* = 71, sleep extension) or a control group (*n* = 71, habitual sleep schedule). The study has one main level of participation (all 142 children) and two additional voluntary levels: substudy-I (*n* = 60; 30 children per group) and substudy-II (up to *n* = 142; 71 children per group).

The study consists of a 12-week active intervention and a 6-month inactive follow-up (i.e., 38 weeks post-randomization). During this inactive follow-up period, no contact with the research team will take place. However, families in the sleep extension group will be instructed to continue putting their child to bed 60–90 min earlier. The overall study design is illustrated in Figure 1. All children will be assessed at three time points: baseline (Visit A), at the end of the active intervention (Visit B, week 12), and at the end of the 6-month follow-up (Visit C). During the intervention period, participants in both groups will attend 6 sessions with a family advisor, combining in-person and virtual formats over 12 weeks, to ensure consistent and equal contact frequency with the research team.

**Figure 1 F1:**
[figure not shown]
Overview of the study design. Children will be screened for eligibility during a screening visit. Randomization will take place after the completion of the baseline visit. There are three assessment visits: **(A)** (baseline), **(B)** (12 weeks), and **(C)** (6-month follow-up). In addition, at the beginning, middle, and end of the active intervention and at the end of follow-up, the children will wear an actigraph, and the parents will complete a sleep diary. Six sessions with a family advisor will be held during the first 12 weeks. Subgroups of participants will participate in substudy-I and/or substudy-II. DIT, diet-induced thermogenesis; DXA, dual-energy x-ray absorptiometry; EEG/EMG, electroencephalography/electromyography; MRI, magnetic resonance imaging; PSG, polysomnography; RMR, resting metabolic rate; TEE, total energy expenditure; VAS, visual analog scale. [Created in BioRender. [name] (2025) https://BioRender.com/a2d6dcr].

### Recruitment and screening

Participants will be recruited from the Capital Region of Denmark and Region Zealand through a multifaceted approach, including the Danish Civil Registration System (CPR registry), social media platforms, dedicated webpages, professional companies, flyer distribution in educational institutions and healthcare facilities, and word-of-mouth.

Following successful prescreening, the participating families will receive detailed written and oral information regarding the study. If they still wish to participate, the children's guardian(s) will sign an informed consent form and a data protection regulation form, including optional consent for future use of data and biological material. Verbal assent from the children will also be obtained. Thereafter, participants will be invited to a screening visit to evaluate the child's eligibility by obtaining anthropometric measurements, parent-reported sleep duration, medical history, and medication use. Provided that the child is eligible, a demographic questionnaire will be completed, and the family will be provided with a wrist-worn accelerometer for the child to wear and a paper-based sleep diary. They are instructed on how the child should wear the device and how to complete the sleep diary (parents on behalf of the child) for 7 days and 8 nights before Visit A. They are also given access to an online diet assessment tool and instructed on how to complete a 3-day food registration for the child during the same period on weekdays.

### Eligibility criteria

This study plans to recruit 142 children aged 6–12 years who are short-sleepers, that is, sleep 9 h/night or less (34, 35). Children will be excluded if they have any genetic, neurological, endocrine, or psychiatric condition that affects growth, metabolism, eating behaviors, cognitive function, or body weight; any sleep-related disorder; or are taking medication that could influence study outcomes. Additional exclusion criteria include an irregular school schedule, participation in other research studies, or neither parent being able to speak and understand Danish or English. If the child lives in two households, participation will be allowed only if both households can adhere to the intervention on school nights. For substudy-II, children will be excluded if they have metal implants and/or claustrophobia.

### Interventions

#### Sleep extension

Children and their parents will participate in a behavioral intervention, guiding the parent(s) to put their children to bed 60–90 min earlier at night while maintaining the same wake-up time in the morning (20, 21, 36). Previous studies have found that this adjustment is feasible and typically results in 40–45 min of additional sleep (21, 36). Parents of the participating children will be advised to alter only their children's bedtime and will not be provided with specific instructions regarding their children's dietary intake or physical and sedentary activity.

The behavioral intervention consists of 6 sessions delivered over a 12-week period. These sessions will be conducted in person or virtually, depending on the family's availability and to accommodate potential illness or other unforeseen circumstances. The first two sessions will take place within the first two weeks of the intervention. In the initial session, information about the child's sleep patterns is gathered, and a new sleep routine plan is developed in collaboration with the child and parent(s). Specifically, a cooperation agreement is established to support adherence to the new sleep routines. As part of this agreement, the family agrees to non-monetary, non-food-based rewards that emphasize quality family time, such as movie nights, board games, and outings that the child can look forward to. Rewards are scheduled to be given in one to two weeks, midway (week 6), and at the end of the intervention (week 12). Families may shift their child's bedtime by 60–90 min immediately or gradually increase the change over one week to reach the 60–90-minute goal. While both the parent(s) and child are involved in establishing the new routine, particular emphasis is placed on the child's wishes to foster a sense of ownership.

The family will receive guidance on sleep hygiene practices and effective behavioral strategies to enhance sleep time. These strategies include goal setting (e.g., bedtimes and wake-up times), self-monitoring using a sleep diary, problem-solving, preplanning, stimulus control (i.e., sleep hygiene recommendations), and positive reinforcement. Families will also be offered pictograms to support consistent bedtime routines, such as putting on pajamas, brushing teeth, reading a book, and turning off the lights. In addition, they will receive guidance on managing common bedtime challenges, such as the child repeatedly leaving his/her bed. They will also be instructed to avoid caffeinated drinks from 1:00 pm and refrain from using screens (e.g., mobile phones, tablets, and TVs) during the hour before bedtime. In the second session, the new sleep routines are evaluated with the family and adjusted, if needed.

The remaining four follow-up sessions will be conducted biweekly to reinforce the routines introduced in the initial sessions. One of these sessions will be held without the child being present, allowing the parent(s) to share their experiences more freely. Throughout these sessions, families will continue to be encouraged to use non-monetary, non-food-based rewards to motivate and foster compliance, with an emphasis on the quality time spent together, such as playing games or reading. The implementation of the new sleep routines will be evaluated at each session, and families will receive positive reinforcement or suggestions for adjustments if any challenges arise.

The final session includes a review of the collaboration agreement established in the initial sessions to evaluate the family's adherence to the agreed-upon routines and rewards. This session will also prepare the family for upcoming assessments and reinforce their continued commitment to follow sleep routines beyond the intervention period. Lastly, parents will also be asked to evaluate the tools and strategies used during the intervention period.

#### Control

The control group families will be instructed to maintain their children's habitual daily sleep routine, allowing diet and physical activity habits to change naturally. To equilibrate the potential influence of contact with the research team, the control group will have the same number and frequency of sessions (in-person and virtual). These sessions will be educational in nature and will focus on the general well-being of children and family relations (i.e., child independence, daily structure and routines in the family, and learning about emotional self-regulation), in addition to informing them about the different assessments at home (sleep diary, accelerometer, dietary registrations, and urine collection).

### Compliance

Compliance will be assessed using both a parent-reported sleep diary that records bedtime, sleep onset time, and wake-up time, and actigraphy data collected via a wrist-worn accelerometer, with the children wearing the accelerometer on the same days as the sleep diary is completed. Compliance is defined as an increase in sleep duration of ≥30 min/night after 12 weeks.

### Data collection and outcomes

The study involves various visits for participating families, including an information meeting, screening, assessment visits A and B (each spanning over 2 days), visit C, sessions with the family advisor, and additional visits for those participating in substudy-I and substudy-II. Data collection follows standard operating procedures and is detailed in Tables 1, 2. Most data are collected during the active intervention period. Participants who discontinue the intervention will be invited to attend an early termination visit. Participants who withdraw from the study during the active intervention will be invited to attend an early termination visit identical to Visit B, whereas those who withdraw during follow-up will be invited to attend a visit identical to Visit C.

**Table 1 T1:** Overview of visits and assessments for the main study.

Method/assessment	Outcomes	At home	Visit A	At home	Visit B	At home	Visit C
		(Week −1)	(Week 0)	(Weeks 1–11)	(Week 12)	(Weeks 13–37)	(Week 38)
Method/assessment	Outcomes						
Anthropometry and metabolic health							
Anthropometric measurements	BMI z-score		X		X		X
DXA	Fat and lean mass and fat percentage, BMD, and BMC		X		X		X
Fasting blood sample	Clinical biochemistry: cardiometabolic risk factors, appetite-regulating hormones, sex hormones, and PBMCs.		X		X		
Puberty status	Tanner stage		X		X		X
Sleep							
Actigraphy	Sleep duration, movements, and awakenings	X		X		X	
Polysomnography	Sleep stages, duration, latency, awakenings, and arousals		X		X		
Stanford Sleepiness Scale	Alertness		X		X		X
Sleep Screen Questionnaire-Children and Adolescents (SSQ-CA)	Sleep duration, latency, awakenings, and tiredness/sleepiness		X		X		X
Learning and brain function							
Track-It and word memory test	Learning ability, including skill learning ability and explicit memory		X		X		
EEG/EMG	Muscle activity during skill learning, corticocortical functional connectivity, and corticomuscular connectivity		X		X		
School performance	Mathematics proficiency and Danish reading comprehension		X		X		X
Motor skills							
Pegboard test and handgrip dynamometer	Fine motor skills and muscular strength (gross motor skills)		X		X		X
Lifestyle behaviors							
3-day dietary record	Total energy intake, energy percentage of carbohydrate, fat, protein, and fiber, and meal timing	X		X		X	
Meal timing diary	Eating window duration	X		X		X	
Actigraphy	Total physical activity and time spent on MVPA	X		X		X	
Well-being and mental health							
KIDSCREEN-27	Total Health Related Quality of Life scores or subscale scores: physical well-being, psychological well-being, autonomy, parent relation, peers and social support, and school environment		X		X		X
Perceived Stress Scale for children (PSS-C)	Perceived child stress		X		X		X
Pediatric Quality of Life Inventory (PedsQL)	Total Health Related Quality of Life and Physical Health Summary score, Psychosocial Health summary score		X		X		X
Strength and Difficulties Questionnaire (SDQ)	Total difficulties score and subscale scores of emotional symptoms, conduct problems, hyperactivity/inattention, relationship problems, and prosocial behavior		X		X		X
Perceived Stress Scale (PSS)	Perceived parental stress		X		X		X

BMI, body mass index; BMC, bone mineral density; DXA, dual-energy x-ray Absorptiometry; EEG/EMG, electroencephalography/electromyography; MVPA, moderate-to-vigorous physical activity; PBMC, peripheral blood mononuclear cells.

**Table 2 T2:** Overview of visits and assessments for substudy-I and substudy-II.

Method/assessment	Outcomes	Visits A and B	Visit B
		(Week 0)	(Week 12)
Method/assessment	Outcomes		
Substudy-I			
Fasting and postprandial blood samples	Clinical biochemistry: cardiometabolic risk factors and appetite-regulating hormones	X	X
Indirect calorimetry	Resting metabolic rate	X	X
	Diet-induced thermogenesis		
Doubly labeled water*	Total energy expenditure	X	X
Image-based appetite rating scale	Fasting and postprandial subjective level of hunger and satiety	X	X
Substudy-II (MRI)			
Structural MRI: MP2RAGE (T1) and T2-weighted imaging	Cortical thickness, volume, surface area, volumes of subcortical gray matter structures, myelination (R1)	X	X
Diffusion-weighted imaging	Brain gray and white matter microstructure	X	X
Resting-state fMRI	Brain functional connectivity	X	X

fMRI, functional magnetic resonance imaging; M2PRAGE: magnetization prepared 2 rapid acquisition gradient echoe.

* DLW urine samples are collected at home over a 14-day period following visits A and B.

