##### Dietary energy intake (main study)

Dietary energy intake and macronutrient consumption (fat, carbohydrate, and protein) will be estimated using averages of 3 days of diet recording, facilitated through an online dietary assessment tool, myfood24.org, which is available in Danish, English, German, French, Spanish, Norwegian, and Arabic, and has been validated for use with children (43). Children and their parents will be asked to record, in chronological order, all foods and drinks consumed over 3 days of the week. This will exclude Friday, Saturday, and Sunday (44) to align dietary intake with sleep duration during the school days. The parents will receive a MyFood24 link on each registration day. In MyFood24, parents can search for Danish and international food items in the Frida Fooddata database (v2 2017.20.02), the Livmedelsverket National Food Agency database, McCance and Widdowson v7, UK general brands, plus Tesco. The parents will be instructed to record dietary intake either as weighed amounts or using image-based portion sizes. For mixed dishes, parents can create recipes and record the portion consumed. Dietary records will be reviewed by study staff upon return and checked for unrealistic intakes or missing information, which will then be clarified with the parents. If no dietary registration has been completed prior to the visits, parents will be asked to complete a new registration within the following week. In addition, the estimated duration of the daily eating window will be assessed by instructing parents to record the times when their child starts and finishes eating on each registration day.

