##### Energy expenditure (substudy-I)

The resting metabolic rate (RMR) and diet-induced thermogenesis (DIT) will be measured using indirect calorimetry (Vyntus CPX, Intramedic A/S, Denmark). The children will come to the laboratory in the fasted state and breathe normally for 25 min under a transparent plastic hood to measure RMR (52). Subsequently, they will consume a standardized breakfast meal (*t* = 0). To estimate DIT, further assessments of energy expenditure will be conducted 45–70 min and 95–120 min after meal ingestion. The size of the test meal will be identical before and after the intervention for all children. If a child does not consume the entire meal at baseline, the leftovers will be weighed, and the meal will be adjusted accordingly after the intervention. DIT will be calculated as the incremental area under the curve of energy expenditure over time and will be expressed as absolute calories (kcal) and percentage of ingested calories (%) (53). Blood samples (10 mL) will be collected in the fasting state and 2 h after the completion of the meal test.

Total energy expenditure (TEE) will be assessed using doubly labeled water (DLW), that is, water enriched with two stable isotopes of oxygen and hydrogen (^18^O and ^2^H) (54–56). On the first day of visits A and B, the children will provide a baseline urine sample and drink 50 mL of DLW. The first post-DLW urine sample will be collected the following morning, and 6 additional urine samples will be collected at home over the next two weeks. The DLW method is based on the differential rates of 2H and 18O excretion to estimate the rate of carbon dioxide (CO_2_) production (57). CO_2_ is the end product of human oxidative metabolism and is thus a direct metric of energy expenditure under free-living conditions (58).

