### Randomization and blinding

After completion of baseline assessments (Visit A), the children will be informed of their group allocation by receiving a sealed envelope. The children will be randomized in a 1:1 ratio to the sleep extension or control group. To ensure balance between the two groups, randomization is stratified by sex (male or female), age (≤9 or >9 years), and participation level (main study only; main+substudy-I; main + substudy-II; main + substudy-I and -II), with each combination defining a stratum. The allocation is determined by a computer-based algorithm implemented in an Excel file. The algorithm is configured such that the probability of allocation depends on the current distribution of participants across groups, thereby maintaining balance between the sleep and control groups and within each stratum. This file is stored as a restricted-access file available only to designated staff for the randomization task. The allocation is subsequently recorded in an electronic case report form within the Research Electronic Data Capture (REDCap) system.

The behavioral nature of the intervention precludes blinding of children and their parents. Nonetheless, staff assessing outcomes and analyzing the data will be blinded to group allocation.

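### The baseline window for total energy expenditure lies mostly after allocation and overlaps the start of the intervention; make-up baseline diet records have the same weakness

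*Protocol article*

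**What the plan says.** All references are to the protocol article.

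- **DLW.** Under Energy expenditure (substudy-I): "On the first day of visits A and B, the children will provide a baseline urine sample and drink 50 mL of DLW". One post-dose sample follows the next morning, and "6 additional urine samples will be collected at home over the next two weeks". The footnote to Table 2 agrees: "DLW urine samples are collected at home over a 14-day period following visits A and B".
- **Allocation.** The legend to Figure 1: "Randomization will take place after the completion of the baseline visit". Randomization and blinding: "After completion of baseline assessments (Visit A), the children will be informed of their group allocation by receiving a sealed envelope". Data collection and outcomes gives Visit A a length of two days, and Table 1 places it at week 0.
- **Clock.** Study design places the end of follow-up 38 weeks after randomization, and Table 1 places Visit C at week 38.
- **Start of the intervention.** Sleep extension: "The first two sessions will take place within the first two weeks of the intervention". The new routine is drawn up in session 1, and families may move bedtime at once or step it up over a week.
- **Diet.** Recruitment and screening and Table 1 place the planned baseline record before Visit A. Dietary energy intake adds a fallback: "If no dietary registration has been completed prior to the visits, parents will be asked to complete a new registration within the following week". Visit A is not excepted.
- **Analysis.** The only model described is a linear mixed model with group, time and their interaction, fitted to baseline and 12 weeks. Energy expenditure and dietary energy intake are both listed as secondary outcomes.

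**The concern.** DLW does not give a reading at one moment. It estimates average expenditure from isotope elimination across the whole sampling period. Dosing before allocation therefore does not make the result a pre-allocation measurement if most of the period comes afterwards. Actigraphy and the planned diet record, by contrast, are collected in the week before Visit A.

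If the new bedtime is in force for part of the baseline period, any early effect on expenditure enters the baseline of the extension arm only. The group-by-time term then subtracts it from the week-12 effect. A null result for total energy expenditure could not be told apart from a contaminated baseline, in an outcome meant to explain how sleep affects weight.

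The diet point is narrower. A make-up baseline record describes the first week after allocation and is completed by parents who know the arm. Reporting or eating could then differ between arms at what the model treats as baseline.

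**Working it through.** **1. Where randomization sits.** The active period is 12 weeks. Visit C at week 38 leaves 38 − 12 = 26 weeks, which matches the 6-month follow-up. Since week 38 is also described as 38 weeks after randomization, randomization is at week 0. The schedule has no two-week gap between Visit A and randomization.

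**2. Share of the window after allocation.** Take the window as 14 days from the dose. Visit A ends 1 to 2 days after dosing, depending on how the two days are counted.
- Allocation at day 1: (14 − 1)/14 = 0.93
- Allocation at day 2: (14 − 2)/14 = 0.86

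So 12 to 13 of 14 days come after allocation.

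**3. Share exposed to the new bedtime.** Let s be the day on which the change starts and f the exposure averaged over the window.
- Immediate shift: f = (14 − s)/14. For s = 2 and 1, f = 0.86 and 0.93.
- One-week ramp, which costs half of 7 days: f = (14 − s − 3.5)/14. For s = 2 and 1, f = 8.5/14 = 0.61 and 9.5/14 = 0.68.
- Start on day 7 (assumed, because session 1 is not dated relative to Visit A): with a ramp f = 3.5/14 = 0.25; with an immediate shift f = 7/14 = 0.50.

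**4. Effect on the contrast.** Let D be the true week-12 effect and q·D the effect in the first two weeks under full exposure. The group-by-time term estimates D − f·q·D, so the share retained is 1 − f·q. The documents give no value for q; 0.25, 0.5 and 1 are illustrations.

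| Start of change | f | q = 0.25 | q = 0.5 | q = 1 |
|---|---|---|---|---|
| Immediate | 0.86–0.93 | 0.77–0.79 | 0.54–0.57 | 0.07–0.14 |
| One-week ramp | 0.61–0.68 | 0.83–0.85 | 0.66–0.70 | 0.32–0.39 |
| Day 7 | 0.25–0.50 | 0.875–0.94 | 0.75–0.875 | 0.50–0.75 |

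If the bedtime change came only after the last baseline sample, f = 0 and nothing would be lost.

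**5. Diet.** A record made up in the week after Visit A falls wholly after Visit A, and so after allocation as scheduled. The planned record does not. The share of make-up records is not stated, so no size can be given.

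**6. What is untouched.** BMI z-score, the learning tests, resting metabolic rate and diet-induced thermogenesis are measured at the visit itself.

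**The case against.** The best defence is that completing the baseline assessments could be read to include the urine collection, so that substudy-I families wait. Figure 1 is not shown and the article condenses a longer protocol, so this cannot be excluded. Against it, the text equates those assessments with Visit A, the legend speaks of the baseline visit, and the week-0 to week-38 clock has no room for a delay. With Visit B at week 12, waiting two weeks would leave 12 − 2 = 10 weeks of intervention. On either reading the statements need reconciling.

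A second objection stands: session 1 is not dated, so exposure to the new bedtime may be well below the share of days after allocation. That is why f is given as a range.

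A reader might also infer four stronger things that the documents do not support:
- **The whole baseline window is on-intervention.** It cannot be, because dosing and the first part of the window precede allocation. Nor is half the window a floor, since that presumes session 1 on the day of Visit A.
- **A true effect is largely cancelled.** That needs a prompt start and a near-full early response (q close to 1), which nothing in the article states.
- **The Visit B window is off-treatment.** It follows the last session, but Study design and Sleep extension say that extension families are to continue the earlier bedtimes.
- **The diet baseline as a whole is compromised.** Only make-up records are.

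Finally, the article calls the substudies exploratory and gives them no power calculation. That limits the weight of the point, but energy expenditure is still listed as a secondary outcome.

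**Conclusion.** The point holds for total energy expenditure in all 60 substudy-I children. As scheduled, 86–93% of the baseline window follows allocation, and the window overlaps the start of the intervention. The first figure rests on allocation at the end of the two-day Visit A. The exposure shares rest further on when the bedtime change begins, which is not stated.

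The direction of the bias is toward zero when the early effect has the same sign as, and is no larger than, the week-12 effect. Its size cannot be given, because the speed of the response is not in the documents. The conclusion also assumes that the mixed model described for the trial is applied to this outcome.

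For diet, the point is confined to make-up baseline records. Neither part touches the co-primary results. The defect should be corrected, but it does not threaten the trial's main conclusions.

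**What to change.** 1. Reconcile the statements on allocation timing, start of the intervention and DLW window, and state for substudy-I when the envelope is opened and session 1 held relative to the last baseline urine sample.
2. Unless allocation is in fact withheld until that sample, do not use the Visit A expenditure as baseline. Compare Visit B expenditure between arms, adjusted for DXA lean and fat mass and resting metabolic rate measured before randomization. Report the Visit A window as early on-intervention expenditure.
3. Set any baseline diet record completed after allocation to missing. The planned mixed model uses all available observations without imputation, so the child's 12-week record is kept. Report the number of such records by arm.

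Items 2 and 3 need only wording and no new samples. The price is some loss of precision for total energy expenditure and some missing diet baselines.

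Delaying allocation for substudy-I is an alternative only if the week clock is restated. Otherwise it shortens the intervention for these children or moves their Visit B, and with it the interval over which their co-primary outcomes are measured.
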